### Outcome measures

#### Primary outcome measures

Rate of change in cognitive performance, as measured by latent variables for the cognitive constructs detailed below.

#### Secondary outcome measures

Change in: MMSE; perceived health status, depressive symptoms, positive and negative affect, life satisfaction, self-reported cognitive functioning, and functional capacity, as assessed by the questionnaires below; blood pressure; biomarkers of glucose, glycated haemoglobin, triglycerides, total cholesterol, HDL, LDL, homocysteine, CRP, MDA, and telomere length.

### Cognitive test battery

No previous definitive evidence suggests which cognitive domains may be amenable to change via *n*-3 LC PUFAs, thus the test battery used in this study comprehensively assessed all relevant domains that might benefit from a nutritional intervention. The focus of the battery was on constructs that are sensitive to age-related changes and that are most strongly associated with functional status, functional decline, and dementia.

Most of the cognitive domains were assessed using tasks in which speed of response was the main outcome measure. The psychometric properties of speed tasks make them more sensitive to subtle cognitive changes and obviate the need for parallel forms for repeated assessment. These properties, together with evidence that processing speed is integral to higher-order processes such as reasoning [43], may be a key indicator of changes in neural efficiency [44] and functional outcomes [45], and is an important mediator of age-related cognitive changes [46], make speed tasks ideal as outcome measures to test the effect of a nutritional intervention on cognitive performance in older-age.

With the exception of two individual tasks, at least two measures of each cognitive construct were used to indicate a latent construct for statistical analyses, thereby reducing task-specific variance and increasing construct validity and the reliability of assessment. The cognitive constructs assessed were Reasoning, Working Memory, Short-term Memory, Retrieval Fluency, Inhibition, Simple and Choice-Reaction Time, Perceptual Speed, Odd-man-out Reaction Time, Speed of Memory Scanning, Psychomotor Speed, Inspection Time, and Knowledge. The latter two were measured by only one task each and the knowledge measure was included as a 'control' task in that the construct it assesses does not decline with age nor would it be expected to be modifiable by intervention. Excepting the tasks measured by speed of response, parallel versions of each task were presented at each assessment visit unless otherwise specified. For a detailed description of the test battery see Appendix 1.

All measures were completed in small groups of up to 7 people, in CSIRO's Cognitive Laboratory, and administered by 2 trained research officers. The testing sessions lasted approximately four hours and consisted of four sections of around 50 min duration, with a break of approximately 10 min between each section. During this break participants were provided with standard refreshments, including decaffeinated tea/coffee. The speed tasks were interspersed between the accuracy based tasks and to also help minimise fatigue, paper and pencil tasks were interspersed with computerised tasks, which were administered in an adjacent room. The order of tasks was fixed across participants and testing sessions. Instructions and practice items preceded each test, and questions were clarified before commencement.

### Participant demographics

At study commencement, a questionnaire ascertained the following demographic and health information: sex, date of birth, and occupation (prior main occupation if retired); diagnosed medical conditions and regularly taken medications; supplement use and duration; and, for women, the use of hormone replacement therapy. A smoking questionnaire assessed current smoking status, the number of cigarettes/cigars/pipes smoked per day, and smoking history, from which pack years was derived (number of pack years = (number of cigarettes smoked per day × number of years smoked)/20) to measure lifetime direct smoking exposure. Changes to smoking habits were captured at study end.

Information was updated regarding medical and health details during the first and then subsequent visits to the CSIRO clinic.

During the assessment sessions, questionnaires were administered to gather other relevant demographic information: highest level of education achieved, country of birth and if relevant, the age of arrival in Australia and years of speaking English, parents' birth country and occupations, perceived ethnicity, cultural determinants of family diet in childhood, familial history of diagnosed dementia, current income level (as per the Australian census, 2006), and relationship status. Frequency of computer use, handedness, and possible hearing and vision impairments (including colour blindness) were also recorded. Participants' level of engagement in day-to-day mental or cognitive activities was assessed by self-reported minutes per week doing challenging puzzles, self-directed learning, managing finances, or teaching/attending classes. At study end participants stated which experimental group they thought they were in, to assess adequacy of blinding.

### Physical activity, functional capacity, and well-being

To assess changes in functional capacity and well-being, and potentially control for any effect of changes in mood or physical activity on cognitive functioning, validated questionnaires assessing everyday functioning (The Late Life Function and Disability Instrument [47,48]), depression (Centre for Epidemiology Studies Depression Scale [49]), self-reported cognitive functioning (Cognitive Failures Questionnaire [50], Prospective and Retrospective Memory Questionnaire [51]), subjective well-being (mood: Positive and Negative Affect Scale-Extended [52]; life satisfaction: Diener's Satisfaction with Life Scale [53], the Personal Wellbeing Index [54]), health-related quality of life (SF-36 [55], the sleep scale from the Nottingham Health Profile [56]), and physical activity (The Yale Physical Activity Survey [57]) were compiled as a general health and wellbeing questionnaire, which participants completed for each assessment. See Appendix 2 for descriptions of the questionnaires and derived scores.

### Dietary Intake

The Victorian Cancer Council FFQ [58,59] was used to measure average daily dietary intake, and a Polyunsaturated Fatty Acid FFQ [60] was used to assess usual dietary intake of *n*-3 and *n*-6 PUFAs. The PUFA FFQ was administered in paper format and scored using the electronic version. Lifetime seafood intake was assessed via the Lifetime Diet Questionnaire [61].

### Anthropometry and blood pressure

Height was measured at baseline, using a wall-mounted stadiometer (SECA, Hamburg, Germany) and weight was measured at each assessment session using a calibrated digital precision scale (UC-321PBT; A&D Medical, Sydney, Australia). Body Mass Index was calculated as weight (kg)/height (m)^2 ^to examine as a potential covariate. Blood pressure was measured in the left arm and after the subject had been seated supine for 5 minutes, using an automated sphygmomanometer (Sure Signs V3; Philips Medical Systems, Andover, MA), and the average of three consecutive readings was used as the measured value for each assessment.

### Biochemical indicators

Blood was collected into Vacutainer tubes containing EDTA, cooled to 4°C and separated into plasma (for malondialdehyde and carotenoids analyses) and erythrocytes (for analysis of fatty acids) by centrifugation. Erythrocytes were washed twice with isotonic saline and reconstituted to the original volume in water to lyse the cells. For glucose analyses, plasma was separated from blood collected into Vacutainer tubes containing EDTA + NaF. Serum was separated from clotted blood for lipid analyses. Aliquots of plasma, serum and lysed erythrocytes were stored at -80°C until analysis.

Serum vitamin B12 and folate, plasma homocysteine, and HbA1c were measured at an accredited pathology laboratory (IMVS, Adelaide, Australia). Plasma glucose and serum total cholesterol, triglycerides, HDL, and CRP were measured on a Hitachi 902 clinical analyser using diagnostic kits (Roche Diagnostics, Australia). LDL cholesterol was calculated using the Friedewald Equation [62]. Plasma MDA was measured by a fluorescence high performance liquid chromatography (HPLC) method as detailed by Belobradjic et al [63].

Carotenoids were measured on a Shimadzu LC10 HPLC fitted with a refrigerated auto sampler and a SPD-MV10 Avp photodiode array detector with a class LC10 chromatography workstation. The chromatographic separations of the fat soluble vitamins and carotenoids were carried out on a Varian Microsorb-MV reverse phase C18 column, 4.6 mm ID × 250 mm length, 5 micron spherical particles [64].

The analysis of erythrocyte membrane fatty acids was based on a method reported by Ridges et al. [65], which uses a one-step extraction and transesterification procedure [66]. Solid phase extraction on florisil (Sigma-Aldrich Pty Ltd, Castle Hill, NSW Australia) was used to clean up the toluene extract containing the fatty acid methyl esters (FAME) after the transesterification procedure. Briefly, the toluene was dried under nitrogen, residue redissolved in hexane and loaded onto florisil. The FAME were eluted from the florisil with 10% ether in hexane, dried under nitrogen and re-dissolved in isooctane. An aliquot was injected onto a bonded-phase vitreous silica BPX70 column 30 m × 0.53 mm × 0.5 micron (SGE, Australia) in an Agilent 6890N gas chromatograph equipped with a cool on-column injector. Peak identification was based on a comparison of retention times with Supelco 37 component FAME mix 47885-U (Sigma-Aldrich Pty Ltd, Castle Hill, NSW Australia) and peak areas were measured using ChemStation software.

### Genomic Markers

ApoE genotyping was performed using Polymerase Chain Reaction (PCR) - Restriction Fragment Length Polymorphism method, as described by Hixson et al. [67]. Absolute telomere length was measured by determining the number of TTAGGG hexamer repeats using quantitative real-time PCR as described by O'Callaghan et al [68].

### Statistical Considerations

#### Analysis

Latent growth curve modelling (LGCM) will be the main analysis method used to assess the effect of the intervention. LGCM is an appropriate and rigorous methodology to employ for intervention studies that aim to alter a developmental trajectory and has greater power to detect an effect than models traditionally used in examining interventions, such as ANCOVA or repeated measures ANOVA [69].

Four equally-spaced testing time points were used in this study because, firstly, four time points are required to distinguish between different growth forms (e.g., linear, quadratic) and, secondly, four time points are estimated to give adequate power. The cognitive domains will be modelled as latent variables, providing the cognitive factors prove to be measuring the same construct across time, following the initial planned modelling of the tasks and cognitive factors on baseline data using confirmatory factor analysis (CFA). The main effect of the intervention on each cognitive domain will initially be assessed separately following Muthèn and Curran [69]. The main intervention effect can be tested by modelling the shape of the curve, for the time-points of a construct, for treatment and control groups separately. Both groups are constrained to the same normative growth trajectory, and the treatment slope added to the treatment group. Statistical significance of the mean of the treatment slope indicates a significant main treatment effect. Within this framework, further tests will also examine interaction effects, to determine whether the magnitude of the treatment effect varies as a function of initial cognitive status, and whether other factors, such as carriage of the ApoE-e4 allele, sex, or initial *n*-3 status, moderate the treatment effect. Similar analyses will be undertaken for well-being.

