## Methods/Design

The primary aim of the current trial was to comprehensively assess over 18-months the efficacy of a DHA-rich fish-oil supplement on slowing cognitive decline in non-demented older adults; the hypothesis was that, over 18 months, the *n*-3 LC PUFA supplementation group would show slower cognitive decline than the control group. The trial was set within the broader context of examining nutritional, health, and lifestyle factors associated with better cognitive and well-being outcomes in the elderly, both cross-sectionally and longitudinally.

Secondary aims were: 1) to explore relationships between measures of *n*-3 LC PUFA intake and measures of cognitive function at baseline; 2) to determine whether the effect of *n*-3 LC PUFA supplementation on cognitive decline is moderated by presence of the ApoE-ε4 allele, initial cognitive status, measures of dietary *n*-3 LC PUFA intake (including changes in *n*-3 LC PUFA status) or any nutritional, health-related, or psychological factors associated with cognitive outcomes in the elderly; 3) to examine the effect of the intervention on measures of functional capacity and well-being; and 4) examine relationships between measures of *n*-3 LC PUFA intake and functional capacity and well-being at baseline.

This paper details the methodology of the study, including the design, assessment battery, and research protocols used.

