### Study design

The trial was a parallel, 18-month, randomised, double-blind, placebo-controlled trial with repeated measures every 6 months, totalling 4 measurement points. Because the primary hypothesis related to change in a continual developmental process, multiple repeated measures enable determination of the rate of change on the measures, allowing assessment of an intervention effect on a trajectory, rather than effects at a specific time point. Decline of the cognitive abilities vulnerable to ageing effects begins by the early 30s so although participants were screened for cognitive impairment, all were expected to experience cognitive decline to some extent; for instance, meta-analyses of cross-sectional data suggest that processing speed declines, on average, by approximately 20% at age 40 and by 40-60% at age 80 [34]. In terms of supplementation duration, studies have detected significant cognitive changes due to *n*-3 PUFA supplementation after 3-4 months [35,36]. However, these studies focused on clinical populations; change in normal populations would not be expected to be as rapid, or of the same magnitude and the longer duration allowed for the multiple testing points required to best test the hypothesis and conferred greater power to detect an effect.

The trial was co-ordinated from CSIRO Food and Nutritional Sciences, Adelaide, Australia. The protocol was explained to participants and written informed consent was obtained prior to study commencement. All experimental procedures were approved by the Human Research Ethics Committee of CSIRO and in compliance with the Helsinki declaration. The study follows Good Clinical Research Practice. Participants were encouraged to inform the trial research officer of any adverse events; these were recorded by the officer. Adverse effects suspected as being related to supplement use were reported to the trial clinical doctor for follow-up. Participants attended the centre every 3 months; every 6 months, to undergo their assessments, and 3-months after each assessment to obtain additional capsules and be followed-up. At these visits, adverse events were recorded, along with any changes in medication, supplement use, or general health.

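### The stated main-effect test is one treatment slope from baseline, which cannot tell slower decline from a one-off gain by month 6 with the same month-18 difference

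*Protocol article*

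**What the plan says.** The Methods/Design section hypothesises that over 18 months the "supplementation group would show slower cognitive decline than the control group". The primary outcome is "Rate of change in cognitive performance, as measured by latent variables for the cognitive constructs detailed below". The Study design section gives the reason for repeated measures as "allowing assessment of an intervention effect on a trajectory, rather than effects at a specific time point".

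The Analysis section describes the main test. The intervention effect can be tested by "modelling the shape of the curve, for the time-points of a construct, for treatment and control groups separately". Then "Both groups are constrained to the same normative growth trajectory, and the treatment slope added to the treatment group", and the decision rule follows: "Statistical significance of the mean of the treatment slope indicates a significant main treatment effect". The other tests named there are interactions and moderators (initial cognitive status, ApoE-ε4, sex, initial n-3 status). The same section justifies four waves partly by the wish to tell linear from quadratic growth.

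The Dietary intervention schedule starts capsules immediately after the baseline assessment. Table 1 places cognitive testing at 0, 6, 12 and 18 months.

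**The concern.** A treatment could produce a given month-18 difference in two quite different ways. In one, decline is slower throughout and the difference between arms grows as 0, D/3, 2D/3, D. In the other, performance is lifted once by month 6 and then declines at the usual rate, so the difference is 0, D, D, D. Only the first is a lasting change in rate.

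An early lift is possible here. The Study design section notes that "studies have detected significant cognitive changes due to" n-3 supplementation after three to four months, though in clinical populations.

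The four waves hold the information needed: between months 6 and 18 the difference stays flat under a lift and widens under slowing. The stated decision rule does not use that contrast. A significant slope could therefore be reported as slowed decline when the rate after month 6 had not changed.

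**Working it through.** **The plan's own power figure.** The Power section gives 0.84 for a total of 350, d = 0.2, alpha 0.05. A plain two-group comparison with 175 per arm (two-sided) gives 0.46 for 0.2 SD and 0.58 for 0.23 SD. The 0.84 is not reproduced. This does not show it to be wrong, because the section defines power as covering the mean and/or the variance of the rate, and residual and treatment-slope variances are not given. The attrition step does reproduce: 350/0.83 = 422, against 420.

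**Model.** From the article: waves t = 0, 1, 2, 3 (six-month units), 1:1 allocation, 175 per arm, equal baseline means, one added treatment slope. Assumed: two-sided 0.05, baseline SD 1, within-person correlation ρ of 0.6 or 0.8, slope variance v between 0 and 0.2 per six-month unit. The covariance between waves is V = ρJ + (1−ρ)I + v·tt′.

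With k = ρ/(1+3ρ), the least-squares results are:
- Fitted slope for a pure step D: D(6 − 18k)/(14 − 36k). It does not depend on v.
- SE² of the single slope: 2(1−ρ)/[n(14 − 36k)] + 2v/n.
- SE² of the months 6-18 slope in a step-plus-slope model: (1−ρ)/n + 2v/n.

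**Fitted slope.**
- ρ = 0.6: k = 0.2143, so (6 − 3.857)/(14 − 7.714) = 0.341 of the step.
- ρ = 0.8: k = 0.2353, so (6 − 4.235)/(14 − 8.471) = 0.319 of the step.
- True slowing to the same month-18 difference gives 0.333.

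**One case by hand** (ρ = 0.6, v = 0, D = 0.2). SE = √[0.8/(175 × 6.286)] = 0.0270. Step: z = 0.0682/0.0270 = 2.53, power 0.72. Slowing: z = 0.0667/0.0270 = 2.47, power 0.70.

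**Range for D = 0.2 SD.** The two middle columns are the chance that the single-slope test is significant. The SE ratio is the months 6-18 slope against the single slope. The last column is the power of the months 6-18 slope for true slowing of 0.2 SD by month 18.

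| ρ | v | Pure step | True slowing | SE ratio | Months 6-18 power |
|---|---|---|---|---|---|
| 0.6 | 0 | 0.72 | 0.70 | 1.77 | 0.29 |
| 0.6 | 0.02 | 0.60 | 0.58 | 1.62 | 0.26 |
| 0.6 | 0.1 | 0.35 | 0.34 | 1.35 | 0.21 |
| 0.6 | 0.2 | 0.24 | 0.23 | 1.23 | 0.17 |
| 0.8 | 0 | 0.88 | 0.91 | 1.66 | 0.50 |
| 0.8 | 0.02 | 0.71 | 0.75 | 1.46 | 0.44 |
| 0.8 | 0.1 | 0.37 | 0.39 | 1.21 | 0.29 |
| 0.8 | 0.2 | 0.23 | 0.25 | 1.13 | 0.21 |

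**Other sizes.** These use intercept variance 1, with slope and residual variances varied.
- Planning slope: if the 20% in the Power section is read as slope variance relative to intercept variance (an assumption), the month-18 difference is 0.23 × √0.2 × 3 = 0.31 SD. A pure step of that size is declared in about 40-48% of trials. Simulated maximum-likelihood fits in one such case gave 41% for the step and 46% for slowing.
- If D is large enough for true slowing to have 0.84 power, a pure step is declared in 78-88% of trials (63-76% if a baseline difference between arms is also fitted).

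**The case against.** The strongest reply is that the Analysis section looks at more than one slope. It models the curve for each arm and has four waves chosen to separate growth forms. A quadratic term in the treated arm alone would reveal a 0.31 SD step with power of about 0.53 to 1.00, depending on the variances. The article is condensed, and the linear form of the added slope is not spelled out. This stands as far as it goes: the data and the modelling could expose an early lift. But the text then holds both arms to one normative trajectory and rests the main effect on the mean of the added slope. No stated rule makes the conclusion depend on the shape of that effect.

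Second, the Study design section expects people without impairment to change more slowly and by less than the clinical groups in which three-to-four-month effects were seen. This also stands. The early lift is a possibility, not the expected pattern.

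Third, the article calls a significant slope a main treatment effect, proposes no extrapolation beyond 18 months, and frames the hypothesis over those 18 months. An arm that ends with less net loss has, in that sense, declined less. This limits the harm, but the hypothesis and primary outcome are still worded as rate.

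A reader might infer that an early lift would usually be declared as slowing. The documents do not support that: for 0.2 SD the rate runs from 23% to 88% over the variances in the table.

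**Conclusion.** The point holds in a limited form. The stated test is a valid test of any effect that builds up or persists, but it does not discriminate between slowing and a lift maintained from month 6. Across the cases in the table the two are declared at rates within about 4 percentage points, with almost the same fitted slope. This rests on a linear added slope, equal baseline means and a lift complete by month 6. The absolute rates rest on assumed variance components.

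A reader might go further and conclude that a positive result could never support slowed decline. That does not follow: arm-specific curves over four waves could support it if they were reported and used. Nor does the lack of an assessment after capsules stop count against the plan, since the hypothesis concerns the 18 months of treatment. The gap is the missing link between the shape of the effect and the wording of the conclusion.

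**What to change.** Keep the treatment-slope test as the primary test of any effect. Before allocation is revealed, specify a secondary model on the same data in which the treatment effect has two parts: a step with loadings 0, 1, 1, 1 and a months 6-18 slope with loadings 0, 0, 1, 2. Report both with confidence intervals, together with the model's estimated arm differences at 6, 12 and 18 months.

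Describe a positive result as continued slowing only to the extent that the months 6-18 slope estimate and its interval support it. If the interval is compatible with both zero and the single-slope estimate, say that the trial cannot distinguish an early maintained gain from slowing. Do not read a non-significant months 6-18 slope as a plateau: its power for 0.2 SD of true slowing is only about 0.17 to 0.5 in the cases above.

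No new data are needed, and each model gains one mean parameter. The cost is precision. The months 6-18 slope has a standard error about 1.1 to 1.8 times that of the single slope, so the answer on shape will often be inconclusive.
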